# Efficacy of five-step shoulder manipulation for rotator cuff-related shoulder pain: protocol for a multicenter randomized controlled trial

**DOI:** 10.1186/s13063-023-07540-5

**Published:** 2023-08-07

**Keywords:** Manipulation, Rotator cuff-related shoulder pain, Five-step shoulder manipulation, Exercises, Randomized controlled trials

## Abstract

**Background:**

Rotator cuff-related shoulder pain (RCRSP) is the most common cause of shoulder disorders. In China, manipulation has been used extensively for the treatment of patients with RCRSP. However, high-quality clinical evidence to support the therapeutic effect of manipulation is still limited.

**Methods:**

A multicenter, participant-, outcome assessor-, and data analyst-blinded, randomized, placebo-controlled trial will be conducted. A total of 280 participants with RCRSP will be recruited from three hospitals and randomly assigned to a five-step shoulder manipulation (FSM) group or a sham manipulation (SM) group. Each group will receive four weekly treatment sessions, with all participants performing exercises at home for 12 weeks. Assessments, namely the Constant–Murley score, visual analog scale, range of motion, and 36-Item Short Form Survey, will be made at baseline, 4, 12, 18, and 24 weeks. Adverse events during the study will also be recorded.

**Discussion:**

This is a pragmatic clinical trial to evaluate the efficacy and safety of FSM in patients with RCRSP. The findings of this study will provide worthy clinical evidence for manual therapy for RCRSP.

**Trial registration:**

China Registered Clinical Trial Registration Center ChiCTR2000037577. Registered on 29 August 2020.

**Supplementary Information:**

The online version contains supplementary material available at 10.1186/s13063-023-07540-5.

## Introduction

### Background and rationale {6a}

Shoulder pain is the third most common type of musculoskeletal disorder, with a point prevalence of up to 26% [1]. Rotator cuff-related shoulder pain (RCRSP) is an all-encompassing term that comprises a spectrum of shoulder conditions, such as subacromial impingement syndrome, rotator cuff tendinopathy, and symptomatic rotator cuff tears [2–4], contributing to over two thirds of the occurrences of shoulder pain [5, 6]. Pain and loss of motion and strength in the shoulder are the most common complaints of RCRSP patients [7], limiting their capacity for self-care and employment [8]. The guidelines recommend conservative management prior to injection or seeking a surgical opinion [7, 9, 10].

Manipulation, as a classical type of conservative intervention, achieves a therapeutic effect by aiming to create balance in the muscles and bones of the human body. Generally, a Chinese medicine practitioner uses their hands or different parts of the body to manipulate a specific part of the patient’s body. In China, manipulation has been used widely for patients with RCRSP. The symptoms of RCRSP are believed to result from an imbalance between the muscles and bones caused by tendon malposition and joint subluxation (International Classification of Diseases (ICD) 11th Revision, code: ICD-11). To achieve balance, we devised a five-step shoulder manipulation (FSM) based on the “muscle and bone balance” theory of traditional Chinese medicine (TCM). Our previous study showed that FSM was beneficial in alleviating pain and improving the function of the shoulder in RCRSP patients [11]; however, the study lacked high-quality clinical evidence, had a limited sample size, and was not randomized. To evaluate the efficacy and safety of FSM for RCRSP, we designed this randomized controlled trial (RCT) to focus on pain and functional recovery in the shoulder, providing clinical support for choosing interventions in real-world clinical practice.

#### Objectives {7}

The objective of this study is to evaluate the efficacy and safety of FSM in the treatment of RCRSP.

#### Trial design {8}

This study is a two-arm parallel group, multicenter, participant-, outcome assessor-, and data analyst-blinded, randomized, placebo-controlled trial with a superiority, which includes outcome assessments at 5 time points (baseline, 4, 12, 18, and 24 weeks) over a 24-week period. All eligible patients will be enrolled in the baseline evaluation and then randomly assigned into two groups on a 1:1 basis. One group will be treated with FSM, and the other with sham manipulation (SM). In parallel, patients in both groups will be required to perform home-based exercise as the basic treatment. During the study, Constant-Murley score (CMS), visual analog scale (VAS), full shoulder range of motion (ROM), and 36-Item Short Form Survey (SF-36) will be evaluated. The independent outcome assessors will be responsible for assessing the outcomes.

## Methods: participants, interventions, and outcomes

### Study setting {9}

A total of 280 individuals with RCRSP will be recruited from three hospitals in China: (1) Shanghai Municipal Hospital of TCM, (2) LongHua Hospital Affiliated to Shanghai University of TCM, and (3) Shanghai GuangHua Hospital of Integrated TCM and Western Medicine. These three hospitals are grade III, class A, teaching hospitals affiliated to Shanghai University of TCM, and they are all located in the center of Shanghai, with convenient transportation, good medical conditions, and plentiful patient resources. These conditions will be conducive to the smooth development of the study.

#### Eligibility criteria {10}

*Inclusion criteria*
✧ Age 40–70 years old;✧ Pain in the anterolateral acromial area or pain with active shoulder elevation [12], with symptoms lasting for more than 3 months;✧ Positive signs in each of the following 4 categories: pain when resisting humeral external rotation or abduction, Jobe test, Hawkins test, Neer test;✧ VAS score ≥ 40 mm.

*Exclusion criteria*
✧ Clinical signs of massive rotator cuff tears (a tear greater than 5 cm in diameter) or the presence of two or more tendon tears [13, 14];✧ Glenohumeral osteoarthritis (OA) or other inflammatory arthritis;✧ Frozen shoulder;✧ Fracture or dislocation of shoulder;✧ Previous neck or shoulder surgery;✧ Osteoporosis;✧ Neurological disorders;✧ Tumor;✧ Pregnancy.

#### Who will take informed consent? {26a}

Before the screening, potentially eligible patients will be informed in detail of the purpose, procedure, potential risks, and benefits of the trial. Eligible patients will have 1 week to fully consider whether to participate in the study and will need to sign two informed consents, one held by the researcher and the other by the patient, if they wish to participate.

#### Additional consent provisions for collection and use of participant data and biological specimens {26b}

N/A. No biological specimens will be involved in this study.

## Interventions

### Explanation for the choice of comparators {6b}

The SM is the control treatment in this study and is a reliable placebo that achieves the effect of inert treatment by applying no thrust and strictly confining the manipulation to the skin surface [15]. SM accurately reflects the efficacy of FSM for RCRSP.

### Intervention description {11a}

Participants will receive FSM or SM in 4 therapy sessions once a week. Both groups will also receive the parallel daily home-based exercise program for 12 weeks.

### Five-step shoulder manipulation

Massage. The therapist stands behind the patient and kneads the sternoclavicular joint on the affected site with the index and middle fingers. The intensity is determined by the patient’s acid reflux sensation, and the pressure continued for 30 s.Abduction. The therapist stands on the shoulder side of patient, assists the patient in abducting the affected shoulder to 90°, and applies appropriate upward and downward forces to allow the patient to engage in static confrontation with the relevant muscle groups resisting contraction for 30 s each time.Release. The therapist stands behind the patient’s shoulder with one hand stabilizing the acromioclavicular joint, and the other hand hooking four fingers into the lower third of the medial edge of the scapula. The therapist passively abducts and adducts the scapula with both hands, reciprocates for 4–5 times.Impact. The therapist stands behind the patient with the elbow flexed approximately 135° and the shoulder slightly prone and then holds the elbow in both hands and repeats transverse movements at an appropriate frequency to relax the shoulder. After complete shoulder relaxation, the therapist quickly lifts the humerus to the glenoid cavity to complete the internal impact of the glenohumeral joint.Shake. The therapist stands on the side of the patient, crosses the right wrist with the patient’s forearm on the affected side, and then shakes the shoulder joint clockwise 3 times and then counterclockwise 3 times.

### Sham manipulation

The patient and therapist positioning will be the same as FSM, and the therapist will hold the position for several seconds, without performing the thrust. The operation is described as follows:The therapist stands behind the patient and kneads the sternoclavicular joint on the affected site with the index and middle fingers. The operation is strictly confined to the surface level without involving the deep joint and lasts for 30 s.The therapist stands on the side of the patient’s shoulder and assists the patient in abducting the affected shoulder to 90°. Maintain this position for 60 s without confrontation.The therapist stands behind the patient’s shoulder with one hand on the acromioclavicular joint and the other hand on the lower third of the medial edge of the scapula. Kneading is strictly confined to the surface level and does not cause joint movement for 30 s.The therapist stands behind the patient with around 135° elbow flexion and slight internal rotation of the shoulder and then holds the elbow with both hands and repeats transverse movements at an appropriation frequency.Repeat step (2).

### Home-based exercise

The home-based exercise consists of 9 sections aimed at increasing the strength of the rotator cuff and scapular muscle. Some exercises require elastic theraband or hand weights to provide resistance, and the amount of resistance will vary depending on the individual. The protocol of the exercise program is as follows:

#### Weeks 1–6: exercises (1), (2), (3), (4), and (5)

Scapular setting. Seated isometric holding of the scapula in the extended and retracted position (5 repetitions, 5 s of each position)Self-resisted isometric external rotation. Standing sideways to a wall, the elbow bent 45°, forearm pushing a towel roll into the wall with taking shoulder into external rotation (5 repetitions, 5 s of contraction each repetition)Active external rotation. Sitting opposite a table, placing the forearm on the table, taking the shoulder into external rotation (2 sets, 10 repetitions)Shoulder shrugs. Standing and elevating the scapula actively then lowering it slowly (2 sets, 10 repetitions)Self-resisted isometric abduction. Standing sideways to a wall, the elbow bent 45° and pushing a towel roll into the wall with taking shoulder into the abduction (5 repetitions, 5 s of contraction each repetition)

#### Weeks 7–12: exercises (1), (6), (7), (8), and (9)

(6)Wall push up. Standing arm distance from the wall, shoulder flexion brings hands and shoulders level, body leaning forwards the wall with shoulders in 45° abduction and pushing away when reaching limit (2 sets, 5 repetitions)(7)Resisted external rotation. Standing, elbow bent 90°, forearm close to abdomen, and grasping the theraband at navel level. Keeping upper arm close to the side of the body, and pulling the theraband with taking shoulder into external rotation (2 sets, 5 repetitions, using theraband)(8)Resisted internal rotation. Standing, elbow bent 90°, forearm at 90° from abdomen, and grasping the theraband at navel level. Keeping upper arm close to the side of the body, and pulling the theraband with taking shoulder into internal rotation (2 sets, 5 repetitions, using theraband)(9)Resisted abduction. Standing with arm down, holding a weight in hand, lifting hand with taking shoulder into abduction (2 sets, 10 repetitions, using the weight)

### Criteria for discontinuing or modifying allocated interventions {11b}

Participants may request to withdraw the study or be withdrawn because of study-related adverse events and withdrawal criteria. If a participant withdraws from the study, the study assistant will interview them about their reasons for leaving and collect their safety data, all of which will be recorded in detail in the case report forms (CRFs). If a participant experiences an adverse event and discontinues the study, the clinician will evaluate the patient’s condition to determine if additional treatment is needed.

### Strategies to improve adherence to interventions {11c}

During the study, registration and treatment will be free of charge. After each intervention, research assistants will help patients make an appointment for the next visit and remind patients of their appointment by phone or WeChat the day before the visit. In addition, an instructional video of home-based exercise, which can be viewed online, will be sent to the patients. Diary cards will also be provided, including the exact date and time of exercise, which patients will be asked to record daily and to present the completed cards to the research assistants for review at each visit.

### Relevant concomitant care permitted or prohibited during the trial {11d}

If unbearable pain occurs during the study, the use of non-steroidal anti-inflammatory drugs will be used on temporarily. The type of medication, dosage, and duration will be recorded in detail. If there is a conflict between non-steroidal anti-inflammatory drug use and follow-up, the follow-up will be delayed until 3 days after discontinuation of the medication.

### Provisions for post-trial care {30}

At the end of the study, patients in the SM group will receive four therapy sessions of FSM free of charge. All participants who complete the study will be able to continue to receive healthcare at their specific clinical trial settings, such as health education and functional exercise instruction. When patients complete the study but are not satisfied with symptom relief, clinicians will offer alternative treatments depending on the patient’s condition, such as medications, acupuncture, glucocorticoid injections, or surgery.

#### Outcomes {12}

Primary and secondary outcomes are presented in Table 1.

**Table 1 Tab1:** Primary and secondary outcomes

	Primary outcome	Secondary outcomes		
Outcome measure	Shoulder function	Shoulder pain	Shoulder range of motion	Quality of life
Method of measurement	Constant-Murley Score [16]	Visual analog scale [17]	Active range of movement of shoulder joint [18]	The 36-Item Short Form Survey [19]
Analysis metric and method of aggregation	Difference in the mean of change from baseline between the two groups			
Time point	4, 12, 18, and 24 weeks. The principal analysis will be performed at 4 and 12 weeks	4, 12, 18, and 24 weeks		

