### Sample size {14}

The sample size is calculated based on our preliminary study, which was completed from November 2021 to February 2022. The prior research compared CMS changes from baseline to the end of 4-week treatment in patients receiving FSM or SM plus home-based exercise. Our previous results showed that CMS increased by 24.32 (μ_r_) in the FSM group and increased by 10.31 (μ_c_) in the SM group, and the standard deviation of the FSM group was 17.84 (*σ*). On the basis of the above data, when 1/3 of the standard deviation of the FSM group is selected for Δ, *α* = 0.025 (single-sided), *Z*_1−0.025_ = 1.96, 1 – *β* = 0.90, *Z*_1−0.10_ = 1.282, and the ratio of the number of subjects between the FSM group and SM group (*K*) = 1, using the following formula, 104 participants are required for each group: $${n}_{c}=\frac{{{\left({Z}_{1-\alpha }+{Z}_{1-\beta }\right)}^{2}\sigma }^{2}\left(1+\frac{1}{K}\right)}{{\left({\mu }_{r}-{\mu }_{c}-\Delta \right)}^{2}}$$$${n}_{r}={Kn }\ _{c}$$

On this basis, considering an estimated dropout rate of 20%, 125 cases will be needed for each group. Additionally, because there are three trial centers in this study, 15 additional cases are required for each group owing to the multicenter design. Therefore, a total of 280 participants will be enrolled in this study, with 140 participants in both the FSM group and the SM group.

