## Statistical methods

### Statistical methods for primary and secondary outcomes {20a}

SPSS V26 (IBM Corp., Armonk, NY, USA) will be used for both data input and analysis. Statistical analysis will be performed as follows. First, descriptive statistics will be used for all outcome measures at each measurement point to summarize the results. For normally and nonnormally distributed measurement data, the mean ± standard deviation, and median, will be used for the statistical description of the degree of trend, and dispersion, respectively. Second, differences in the mean change in primary and secondary outcomes from baseline to each time point between the groups will be compared using two independent samples *t*-tests or the Mann–Whitney *U*-test. Finally, chi-square tests will be used for blind evaluation. Statistical significance will be set at a *p*-value < 0.05 (two-sided). Table 3 summarizes the statistical analysis of primary and secondary outcomes.

**Table 3 Tab3:** Variables, measures, and methods for statistical analysis of primary and secondary outcomes

Variable/outcome	Outcome measure	Methods of analysis
1) Primary		
The mean of change in shoulder function from baseline to 4, 12, 18, and 24 weeks	Constant-Murley score (continuous)	*T*-test or Mann–Whitney *U*-test^a^
2) Secondary		
The mean of change in shoulder pain from baseline to 4, 12, 18, and 24 weeks	Visual analogue scale (continuous)	*T*-test or Mann–Whitney *U*-test^a^
The mean of change in shoulder range of motion from baseline to 4, 12, 18, and 24 weeks	Active range of movement of shoulder joint (continuous)	*T*-test or Mann–Whitney *U*-test^a^
The mean of change in quality of life from baseline to 4, 12, 18, and 24 weeks	The 36-Item Short Form Survey (continuous)	*T*-test or Mann–Whitney *U*-test^a^

^a^For data conforming to normal distribution, *T*-test is used, and for data not conforming to normal distribution, Mann–Whitney *U*-test test is used

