## Discussion

RCRSP is a growing worldwide health problem that causes shoulder pain and completely or partially stiffness. Increasing evidence has shown that dynamic constriction of the subacromial space with compression of the subacromial soft tissues is considered to be the key cause of chronic RCRSP [21–23]. Patients with RCRSP usually have tight shoulder muscles and joint capsule, which, in turn, may cause abnormal kinematics of the humerus, scapula, and clavicle, resulting in narrowing of the subacromial space and compression of the soft tissue through it. Therefore, the restoration of subacromial space stenosis is a therapeutic goal for RCRSP treatment. Anatomically, the activity of the shoulder joint includes the coordination of glenohumeral, scapothoracic jiont, sternoclavicular, and acromioclavicular four joints [24]. Previous studies have proven that manipulation therapy can effectively promote the rehabilitation of RCRSP, implying that manipulation is an alternative treatment for RCRSP [25, 26]. Despite the fact that the obvious therapeutic modalities predominantly include glenohumeral or scapulothoracic joint mobilization, spinal manipulation, and soft tissue release [26], we created the FSM to address four joints associated with shoulder motion, trying to quickly regain joint coordination and relieve subacromial soft tissue compression. We hypothesize that individuals using FSM will achieve faster improvements in symptoms and functional limitations compared with those who receive the sham manipulation. Therefore, a randomized, participant-, outcome assessor-, and data analyst-blinded, placebo-controlled study is required to confirm the efficacy of FSM in treating RCRSP.

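### The primary outcome has two principal visits, each tested at an undivided 0.05, with no rule for success; if either visit suffices, the false-positive rate is about 7–10%

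*Protocol article*

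**What the plan says.** Four places in the protocol article bear on which comparison is the primary one.

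- **Outcomes {12}, Table 1.** CMS is the only primary outcome. It is measured at weeks 4, 12, 18 and 24, and the cell then narrows this: "The principal analysis will be performed at 4 and 12 weeks".
- **Statistical methods {20a}, Table 3.** The entry under the primary heading reads "The mean of change in shoulder function from baseline to 4, 12, 18, and 24 weeks". The narrowing to weeks 4 and 12 is not repeated.
- **Statistical methods {20a}, text.** Mean changes "from baseline to each time point between the groups will be compared using two independent samples *t*-tests or the Mann–Whitney *U*-test". One threshold serves every test: "Statistical significance will be set at a *p*-value < 0.05 (two-sided". No order of testing, division of alpha or joint-success rule is stated.
- **Sample size {14}.** The planning data concern one visit: "The prior research compared CMS changes from baseline to the end of 4-week treatment". The calculation uses one-sided alpha 0.025, undivided, and 90% power.

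The Discussion gives the hypothesis: "We hypothesize that individuals using FSM will achieve faster improvements in symptoms and functional limitations". It names no visit.

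**The concern.** A confirmatory trial needs one statement of what counts as a positive primary result. Here two visits are called principal, each has its own test at the full 0.05, and nothing says how the two results combine. Three outcomes are therefore open to choice after the data are seen: success at week 4, success at week 12, or success at both. The first two together give two chances at a positive claim, so the 5% level no longer describes the primary conclusion. The third controls error, but the sample size was not worked out for it. Table 3 adds doubt about whether weeks 18 and 24 are also primary.

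**Working it through.** **1. The plan's own figure.** Sample size {14} gives "CMS increased by 24.32 (μ_r_) in the FSM group and increased by 10.31 (μ_c_) in the SM group", an SD of 17.84, Δ equal to one third of that SD, Z values 1.96 and 1.282, and K = 1.

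- Difference: 24.32 − 10.31 = 14.01
- Δ: 17.84 / 3 = 5.95
- n per group = (1.96 + 1.282)² × 17.84² × 2 / (14.01 − 5.95)² ≈ 102.9, so 103

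The plan states 104, which agrees closely. The calculation has room for one comparison, at week 4, with no alpha shared with week 12.

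**2. Error if either principal visit suffices.** For two tests at two-sided 0.05 under no effect at either visit:

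P(at least one significant) = 0.05 + 0.05 − P(both significant)

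For independent tests this is 1 − 0.95² = 9.75%. For correlated tests the value depends on the correlation between the two test statistics. The article gives none, so a range is assumed. Both changes come from the same patients and share a baseline, so a correlation of about 0.5 or more is plausible. Simulation with 4 million draws per setting gives:

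| Assumed correlation | Any significant, two-sided | Any significant, favouring FSM |
|---|---|---|
| 0 | 9.75% (exact) | 4.9% |
| 0.5 | 9.1% | 4.5% |
| 0.7 | 8.3% | 4.2% |
| 0.9 | 7.0% | 3.5% |
| Single test, for reference | 5% | 2.5% |

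**3. Error if all four Table 3 visits were primary.** With equal correlations among the four tests, the two-sided rate is 15.6% at 0.5, 13.0% at 0.7 and 9.4% at 0.9.

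**4. Error if both principal visits must succeed.** With no effect at either visit, both tests are significant in 0.25% of trials at correlation 0, 0.9% at 0.5 and 2.2% at 0.8. With a real effect at only one visit, the rate cannot exceed the 5% of the other test. Error is therefore at or below 5%.

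**5. Power if both must succeed.** The article gives no week-12 difference or SD, so joint power cannot be computed. A partial check is possible.

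- Evaluable per group after 20% dropout: 140 × 0.8 = 112
- Standard error of the difference: 17.84 × √(2/112) = 2.38
- Week 4, tested against zero: 14.01 / 2.38 ≈ 5.9 standard errors, power above 99.9%
- Week 12, assuming the same SD: 90% power at (1.96 + 1.282) × 2.38 ≈ 7.7 points, which is 7.7 / 14.01 = 55% of the assumed week-4 difference

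Joint power would thus depend almost wholly on the week-12 effect.

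**The case against.** The strongest reply is that Tables 1 and 3 do not truly conflict. Table 1 also lists four visits and then says which two are principal. Table 3 exists to show the test for each variable and has the same form for every outcome; it leaves out the narrowing but does not withdraw it. This stands. A reader might infer from Table 3 that there are four primary tests and an error rate up to 1 − 0.95⁴ = 18.5%. The documents do not support that as the headline: it sets aside the explicit sentence in Table 1 and needs four independent tests, which is not credible for repeated changes in the same patients.

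Second, the inflation is conditional. No sentence says that one significant visit makes the trial positive, and requiring both would hold error at or below 5%. This also stands, but the article does not state that rule either.

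Third, a reader might infer that the 90% power is lost if both visits are required. That is not shown. Week-12 power is unstated, and the partial check above suggests that it could be ample, because the sizing subtracts a margin that the planned test against zero does not use.

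Fourth, a multiplicity rule is often left to a statistical analysis plan, which is not shown here. Its absence alone would be no finding. What remains is what the article itself fixes: two principal visits, a differing list in Table 3, and a single undivided threshold.

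Finally, week 12 has a case of its own, since the home exercise given to both groups runs for 12 weeks. Putting week 4 first is therefore a choice, though it is the one that the sample size already made.

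**Conclusion.** The point holds in this form: two principal visits, each tested at an undivided two-sided 0.05, with no rule for combining them and a sample size built on one of them. If success at either visit counts, the two-sided false-positive rate of the primary claim is about 7–10%, with 9.75% as the independent-tests value. About half of this favours FSM, against a nominal 2.5%. The result rests on the either-visit reading and on assumed correlations of 0 to 0.9.

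A higher rate, about 9–16% at correlations of 0.5 to 0.9, would apply only if all four Table 3 visits were treated as primary, which Table 1 argues against. If both principal visits must succeed, the error is controlled and the joint power is simply not established.

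**What to change.** Before the first unblinding described under Data management {19}, when the data are split by group:

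1. Name CMS change at week 4 as the primary test, at two-sided 0.05.
2. Test CMS change at week 12 at two-sided 0.05 only if week 4 is significant.
3. Label CMS at weeks 18 and 24 as secondary.
4. Make Table 3 and the statistical methods text agree with Table 1 as revised.

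This holds the error over the two principal tests at 5%, needs no more patients and costs no power at week 4. The cost is wording, with the ethics re-approval and registration update that the amendment section {25} requires. The downside is that no week-12 claim can be made if week 4 fails.

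Two alternatives also control the error:

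- **Both visits must be significant at 0.05.** This needs a stated week-12 effect so that joint power can be assessed.
- **Two-sided 0.025 at each visit.** With the plan's Δ this needs 122 evaluable per group for 90% power per test at the assumed week-4 effect and SD. With 112 evaluable, power per test would be 87.3%.

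Any of the three would do, provided that it is written down in advance.
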